## Abstract

**Background:**

Despite declines over recent years, youth tobacco and other substance use rates remain high. Latino youth are at equal or increased risk for lifetime tobacco, alcohol, marijuana, and other illicit drug use compared with their white peers. Family plays an important and influential role in the lives of youth, and longitudinal research suggests that improving parenting skills may reduce youth substance use. However, few interventions are oriented towards immigrant Latino families, and none have been developed and evaluated using a community-based participatory research (CBPR) process that may increase the effectiveness and sustainability of such projects. Therefore, using CBPR principles, we developed a randomized clinical trial to assess the efficacy of a family-skills training intervention to prevent tobacco and other substance use intentions in Latino youth.

**Methods/Design:**

In collaboration with seven Latino community-serving agencies, we will recruit and randomize 336 immigrant families, into intervention or delayed treatment conditions. The primary outcome is youth intention to smoke 6 months post intervention. The intervention consists of eight parent and four youth sessions targeting parenting skills and parent–youth relational factors associated with lower smoking and other substance use in youth.

**Discussion:**

We present the study protocol for a family intervention using a CBPR randomized clinical trial to prevent smoking among Latino youth. The results of this trial will contribute to the limited information on effective and sustainable primary prevention programs for tobacco and other substance use directed at the growing US Latino communities.

**Trial registration:**

ClinicalTrials.gov: NCT01442753

## Background

The American Cancer Society has described cigarette smoking as the most preventable cause of premature death in the United States
[1]. While smoking rates have declined among youth in the US over recent years, in 2005 one-half of all youth had tried cigarettes by the 12th grade
[2]. Further, point prevalence data indicate that 8% of middle school students and 23% of high school students are current smokers
[3]. Alcohol and illicit drug use have also decreased in recent years, but again remain at unacceptably high rates. That is, 75% of students have consumed more than a few sips of alcohol, and one-half have tried an illicit drug by the end of high school
[2].

National data suggest that, compared with whites, middle-school-aged Latino adolescents are at equal or increased risk for lifetime tobacco, alcohol, marijuana, and other illicit drug use
[2,4]. However, considering that the majority of Latino youth are first or second generation
[5], and that rates of tobacco, alcohol, and other drug use increase in Latino youth with greater time in the US
[6-8], rates of tobacco and other substance use will probably rise in future years without prevention efforts.

Protective effects against tobacco and other substance use seen in immigrant adolescents may be conferred by the norms, values, and behaviors that their parents bring from their countries of origin. For example, researchers have identified the traditional Latino value of familism – belief in the importance of family, including extended family
[9] – as protective against alcohol use in youth
[6,10]. Broader research on adolescent health suggests that parents have an important impact on their health behaviors
[11], particularly among ethnic diverse groups
[12,13]. Relationship characteristics, such as warmth, support, and acceptance, and parenting practices such as monitoring, discipline, and positive communication, protect against future tobacco, alcohol, and illicit drug use
[11,14,15], and may be even stronger predictors of substance use for adolescents from diverse ethnicities
[16]. However the quality of relationships and parenting practices are affected by immigration factors, which in turn affect youth substance use
[17,18].

Because characteristics of the parent–youth relationship and parenting practices are associated with tobacco and other substance use outcomes, these family factors are common targets of parent training interventions
[19]. The parent training interventions addressing these factors have shown a positive impact on predictor variables of tobacco and other substance use, such as increased parent involvement, child social competence, and child self-regulation, and on preventing and reducing adolescent tobacco, alcohol, marijuana and other substance use
[20-22]. These interventions have the benefit of both enhancing protective factors and reducing risk
[23,24].

While family-skills training programs have proven efficacious at preventing substance use, there continue to be challenges to widespread uptake of evidence-based programs
[22]. One concern is that efficacy studies are often conducted in highly controlled conditions that may not attend to preferences or values of local communities, may not be feasible to replicate or sustain in community settings, and are delivered under conditions fundamentally different from practice environments
[25]. Community-based participatory research (CBPR) approaches, which recognize the strengths, knowledge, expertise, and resources of communities, and so engage community members in the research process as full partners, may address these concerns by increasing the relevance, feasibility and cultural appropriateness of interventions
[26-28]. Participatory approaches have also been suggested to improve the representativeness and to enhance the implementation of interventions by increasing the relevance and acceptability of intervention approaches and the methods and quality of delivery
[29,30]. Although other family-skills training programs exist for Latino families, to our knowledge none have been developed using explicit CBPR principles in collaboration with organizations who would be probable end-users of the program
[24,31].

Therefore, using a CBPR approach, we developed Padres Informados/Jóvenes Preparados (PI/JP) with the goal of preventing Latino youth substance use by improving parenting practices, parent–youth interpersonal skills, and youth social competencies. Throughout this paper we will refer to the heterogeneous population with heritage from South America, Central America, Mexico, and the Spanish-speaking Caribbean as Latino. Our community collaborative board recognizes that this label does not represent the diversity of ethnicities and ethnic identities held by people from these regions, but selected Latino as the most inclusive and commonly used term available. Here we describe the protocol to evaluate the program’s efficacy in preventing tobacco and other substance use intentions in middle-school-age Latino youth. Our outcome hypotheses are that, at 6 months post intervention, youth in the intervention arm will have statistically significant lower intention to use tobacco, alcohol, marijuana and other drugs, and their participant parents will have significantly better scores on parent–youth relationship and parenting practice measures compared with control adolescents and parents.

## Methods/Design

Based on social cognitive and human ecology theories, PI/JP was designed by a community collaborative board of university and community partners and a parent advisory board of Latino parents of youth (Figure
1). The process began with the parent advisory board, who identified core cultural values that informed their parenting practices and key parenting priorities. In addition, community collaborators directed decisions regarding feasibility of the intervention including limiting the program number of sessions, assuring accessible format and content, and, due to the locally limited number of bilingual/bicultural professionals, having the program delivered by professionals or experienced paraprofessionals. The community collaborative board spent 2 years developing the eight-session curriculum integrating parent and community priorities and practical family education strategies with theoretical behavior change models. Later, a pilot study was successfully conducted to evaluate feasibility of the training program and to make final curriculum changes
[32].

**Figure 1 F1:**
[figure not shown]
**Padres Informados/Jóvenes Preparados conceptual model.** *Intervention components in gray.

The community collaborative board was expanded to include seven participating community agencies: five urban and two rural agencies, including two clinics, a school, three social service agencies and a University of Minnesota Extension site. Agencies serve a largely Latino constituency and hold reputations as trusted service providers. All agencies agreed to participate in the planning, implementation, and evaluation of the project as is consistent with CBPR principles
[33].

The study will proceed through a planning and training phase (year 1), a serial implementation phase (years 2 to 4), and a data analysis and dissemination phase (year 5). To increase community capacity for supporting family-skills training and participating in future research collaborations, collaborating agencies are responsible for recruitment of participants and delivery of the intervention. Therefore, each collaborative site will select two staff to directly participate in the project: one to recruit and coordinate program activities, and a second to deliver the intervention. Community collaborators will be prepared for their roles through extensive training in protection of research participants’ confidentiality, the content of the program, and the theoretical background and practical skills needed for intervention implementation. Criteria for site-facilitators who will deliver the intervention include: preference for degree in education, psychology/therapy, or social work, but left to the discretion of site; at least 3 years of experience providing direct service to Latino families; and bicultural and bilingual in English/Spanish.

### Design overview

We will conduct a randomized controlled trial (RCT) with a delayed treatment condition for the control group (Figure
2) to evaluate the efficacy of the PI/JP family skills training program at preventing tobacco and other substance use intentions in Latino youth. As has been true in other participatory studies, a delayed control trial was determined by community partners to be more acceptable than a traditional RCT
[34].

**Figure 2 F2:**
[figure not shown]
Padres Informados/Jóvenes Preparados study design.

Participants will be enrolled from the seven collaborating agencies. Recruitment will be facilitated by the community agencies with support from the university research team. Family eligibility criteria are listed in Table
1. Randomization will occur at the level of the family with a goal of enrolling 336 families (one youth aged 10 to 14 and at least one parent/guardian) into the study. Families assigned to the intervention condition will receive the family-skills training immediately, while those in the control condition will receive the training approximately 6 months after the first group. To limit the possibility of contamination, facilitators are directed to not utilize materials or procedures outside the study, and parents are asked to not discuss study content with anyone other than a co-parent.

**Table 1 T1:** Eligibility criteria for participants

**Inclusion criteria**	
Parent	
	Either mother or father born in a Latin American country
	Speaks Spanish
	Willing to give consent for self and youth
Youth	
	Between ages 10 and 14
	Speaks English or Spanish
	Identifies himself/herself as Latino/Latina
	Willing to give assent
**Exclusion criteria**	
	Mental disorder incompatible with the participation on the trial
	Prior participation in Padres Informados/Jóvenes Preparados pilot or planning

The primary outcome is intention to use cigarettes in the participating youth, which will be operationalized as susceptibility to smoking assessed among never-smokers and puffers from their responses to three questions (never-smokers) or two questions (puffers)
[35,36]. These questions are: ‘Do you think you will try a cigarette soon?’ (not asked of puffers), ‘Do you think you will be smoking cigarettes one year from now?’, and ‘If one of your best friends were to offer you a cigarette, would you smoke it?’ A never-smoker will be considered nonsusceptible if the answer to the first question is ‘no’ and answers to the both the second and third questions are ‘definitely not’; a puffer will be considered nonsusceptible if answers to the second and third questions are ‘definitely not’. Additional outcomes of alcohol, marijuana and other substance intentions, and past 30-day use of all substances will be assessed through items previously used with middle-school-aged Latino youth
[37,38]. Secondary outcomes include parenting practice and parent–youth interpersonal relational measures that are known to be important predictors of substance use among youth. Table
2 presents the instruments used to evaluate each outcome. We chose scales with established reliability and validity, availability in Spanish, and that were appropriate for low-literacy groups. Most scales include parallel items to be completed by both parents and youth. Bilingual data collectors will lead group interviews using paper-and-pencil surveys with adults and self-administered computer-assisted survey interviewing with youth.

**Table 2 T2:** Instruments used to measure parenting practices and parent–youth relationships

**Scale**	**Cronbach’s alpha in Mexican/Latino population (reference)**
Parenting practices	
Parental Monitoring Knowledge	0.78 to 0.82 [39-41]
Parental Acceptance	0.67 to 0.79 [42]
Consistent Discipline	0.69 to 0.77 [43]
Parenting Practices Self-efficacy	0.86 to 0.94 [44]
Multidimensional Scale of Perceived Social Support	0.93 to 0.86 [45-49]
Parent–youth relationships	
Parent**–**Youth Positive Attachment	0.81 to 0.85 [50]
Adolescent Parent–Child Conflict/Conflict Processes	0.87 to 0.92 [51]

Incentives for participation for parents and youth will be tied to data collection points. Parents will be offered $30 and youth $25 dollar gift cards upon completion of each survey, independent of their participation in the intervention.

This protocol and the corresponding consent forms were approved by the Institutional Review Board of the University of Minnesota (HS# 1008S86938) and the Hennepin County Medical Center Institutional Review Board (HSR# 11–3409).

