#### Missing data strategies for primary and secondary outcomes

Only youth with 6-month post-intervention susceptibility responses will be included in the logistic regression analysis of the primary outcome as there is no reliable method to impute data for this outcome. Multiple imputations will be used for secondary outcomes for subjects with ≤45% of items missing on a given scale. Comparisons of baseline characteristics between study completers and those lost to follow-up will be performed using chi-square tests and two-sample *t*-tests. In addition, sensitivity analyses of the primary outcome will be performed to assess the robustness of intervention effect estimates under a variety of possible attrition bias scenarios
[57].

Finally, according to CBPR we will involve the community partners in the result interpretation process. Together we will formulate a dissemination plan to return results to other interested community agencies, study participants, and the larger community.

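### As written, a youth who smokes beyond puffing at 6 months has no primary outcome value and drops out of the randomised comparison; the resulting bias can go either way

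*Protocol article*

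**What the plan says.** The primary outcome is set out in the protocol article, Design overview, in the paragraph after Table 1. Intention to smoke is operationalised as "susceptibility to smoking assessed among never-smokers and puffers from their responses to three questions (never-smokers) or two questions (puffers"). There are two scoring rules:

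- A never-smoker must pass all three questions to be nonsusceptible.
- For the other class, "a puffer will be considered nonsusceptible if answers to the second and third questions are" both at the firmest level of refusal. The question about trying a cigarette soon is not put to puffers.

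There is no rule for a youth who smokes more than that. Table 1 has no smoking-status criterion, so such youth may also be present at baseline.

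The section on missing data fixes the analysis set: "Only youth with 6-month post-intervention susceptibility responses will be included in the logistic regression analysis of the primary outcome". The reason given is that "there is no reliable method to impute data for this outcome". Sensitivity analyses are planned to "assess the robustness of intervention effect estimates under a variety of possible attrition bias scenarios". Smoking behaviour is measured separately, as an additional outcome: "past 30-day use of all substances will be assessed through items previously used with middle-school-aged Latino youth".

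**The concern.** The outcome definition and the analysis set each look reasonable alone. Together they make entry to the primary analysis depend on smoking status, and on the natural reading that is status at 6 months. The Discussion names smoking initiation as what the programme is finally meant to affect. The intervention may therefore change who is scored, and the youth left unscored are those with the worst result.

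If that happens, the logistic regression no longer compares the groups as randomised. A youth who answers the 6-month survey as a smoker is neither lost to follow-up nor counted as susceptible. The odds ratio can move in either direction, depending on how uptake differs between arms.

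A smaller matter follows from the two scoring rules. If status is taken at 6 months, a never-smoker who was positive only on the question about trying a cigarette soon, and who then tried one, is judged on the other two questions and may be scored nonsusceptible.

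**Working it through.** **Inputs from the article (Sample size and power).** Control rate at 6 months: 22% + 6% = 28%. Intervention rate: 22% − 8% = 14%. Two-sided alpha 0.05, 140 per group, 80% power, 336 families, 18% loss. Retained per arm: 336 × 0.82 / 2 = 137.8, taken as 138.

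**The plan's own figure.** For 28% v 14% at 80% power, the pooled two-proportion formula needs 132 per group, or 146 with continuity correction; the stated 140 lies between them. Pooled power is 82.4% at 140 per group and 81.8% at 138. The planned odds ratio (control v intervention) is (0.28/0.72) / (0.14/0.86) = 2.39.

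**Assumptions.** Let F be the proportion susceptible or smoking, set to 28% v 14%, and let s be the proportion smoking beyond puffing at 6 months. The article gives no value for s, so a range is used.

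**Formulas.** If smokers are dropped, the scored rate is (F − s)/(1 − s), the number analysed is 138 × (1 − s), and the odds are (F − s)/(1 − F). Hence

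OR = [(F_c − s_c)/(F_t − s_t)] × [(1 − F_t)/(1 − F_c)].

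The OR is unchanged when s_c/s_t = F_c/F_t = 0.28/0.14 = 2. It is understated when the uptake ratio exceeds 2 and overstated when it is below 2.

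**Example, 4% v 1%.** Control: (0.28 − 0.04)/0.96 = 0.250. Intervention: (0.14 − 0.01)/0.99 = 0.131. OR = (0.24/0.13) × (0.86/0.72) = 2.21.

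| Uptake, control v intervention (assumed) | Scored rates | OR | Power |
|---|---|---|---|
| none | 28.0% v 14.0% | 2.39 | 81.8% |
| 2% v 1% | 26.5% v 13.1% | 2.39 | 79.5% |
| 4% v 1% | 25.0% v 13.1% | 2.21 | 70% |
| 5% v 0% | 24.2% v 14.0% | 1.96 | 57% |
| 4% v 4% | 25.0% v 10.4% | 2.87 | 88% |

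**No difference in F (28% in both arms).** Uptake of 5% v 1% gives scored rates of (0.28 − 0.05)/0.95 = 24.2% v (0.28 − 0.01)/0.99 = 27.3%, so an arm with less smoking looks worse. Uptake of 2% v 6% gives (0.28 − 0.02)/0.98 = 26.5% v (0.28 − 0.06)/0.94 = 23.4%, an apparent benefit of 3.1 points.

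**Puffer rule alone.** Suppose 1% of control and 0.5% of intervention youth are rescored as nonsusceptible (assumed). The rates become 27.0% v 13.5% and power at 138 per arm is 80.0%. Only youth positive on the first question alone can be affected.

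**The case against.** **Exclusion is nowhere stated.** A reader might infer that the plan says outright that new smokers are removed. It does not. The article is silent on when status is taken, and if status were fixed at baseline a new smoker could still be asked and scored. A full protocol or analysis plan might also class such youth as susceptible. This stands as a limit on certainty. It does not remove the point, because the article states both the scoring classes and the analysis set, and followed literally they leave these youth without a value.

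**Other parts of the plan cover it.** Only partly. The sensitivity analyses concern attrition, and a smoker who completes the survey has not been lost. Past 30-day use would show smoking, but outside the primary comparison.

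**The outcome is intention, not behaviour.** True, and counting smokers as susceptible adds a behavioural element. The alternative, however, is to condition on behaviour after randomisation.

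**The size depends on chosen inputs.** This stands. Uptake beyond puffing over 6 months at ages 10 to 14 may be low, and 2% v 1% costs almost nothing. If 28% v 14% are instead the rates among scored youth, dropping 4% and 1% leaves power at 80.9%.

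**Stronger readings that do not hold.** One might conclude that a programme which prevents initiation always has its benefit understated. On the planned odds-ratio scale that requires uptake to fall proportionally more than overall failure. One might also fear a false benefit. The example above needs three times as much smoking in the intervention arm, and even then the chance of a significant result is only about 8%.

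**Conclusion.** The point holds as a defect in how the primary outcome and its analysis set fit together. Followed as written, a youth smoking beyond puffing at 6 months is left out because of a status that the programme aims to change, and no other part of the article repairs this. That reading is an inference from two sections, since the timing of smoking status is not given.

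Neither direction nor size can be settled from the article. Over the assumed uptake rates in the table, the odds ratio runs from 1.96 to 2.87 against a planned 2.39, and power from 57% to 88%. With low uptake in proportion to the planned rates, the effect is negligible. These figures rest on treating 28% v 14% as rates of being susceptible or smoking, with 138 per arm. They do not show that the stated sample size is wrong.

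The shorter rule for new puffers is minor. The first question does not sensibly apply to someone who has already tried a cigarette, so the rule does not justify treating every new puffer as a failure in the primary analysis.

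**What to change.** - State when smoking status is taken, and define the primary analysis population by baseline status: never-smokers and puffers at baseline.
- Count any such youth who is followed up and smoking beyond puffing at 6 months as susceptible. Survey routing already separates puffers from never-smokers, and past 30-day use is collected, so no new data should be needed.
- Classify smokers in the same way at the post-baseline waves of the trajectory model in Data analysis.
- Keep the published index, among those still never-smokers or puffers, as a sensitivity analysis. Add a second that counts never-smokers who became puffers as susceptible.

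The cost is a change of wording and some recoding. The endpoint becomes a slight composite of intention and behaviour, so the planning rates of 22%, 28% and 14% should be checked against the new definition. Trial status reports that follow-up data collection is under way at some agencies, so the change should be documented, with its reason, before any analysis.
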